### Interim analyses {21b}

This study does not have pre-planned interim analyses or stopping guidelines.

#### Methods for additional analyses (e.g. subgroup analyses) {20b}

No additional subgroup analyses are preplanned.

### Methods in analysis to handle protocol non-adherence and any statistical methods to handle missing data {20c}

Examination of baseline differences on key variables between completers and lost-to-follow-up will be conducted to inform the nature of missing longitudinal data. Methods of examining missing data, e.g., propensity scores, EM algorithm and multiple imputation sensitivity analyses will be considered if necessary. A specific imputation approach, e.g., Markov Chain Monte Carlo will be used, depending on the amount and pattern of missing data. SAS Proc Multiple Imputation and MIAnalyze will be used for these analyses.

### Plans to give access to the full protocol, participant level-data, and statistical code {31c}

The full study protocol is available on clinicaltrials.gov— NCT05174286. The data analyzed will be made available on reasonable request to the corresponding author.

## Oversight and Monitoring

### Composition of the coordinating center and trial steering committee {5d}

The coordinating center and trial steering committee include the following members: the Contact-Principal Investigator (Columbia University, Dept. of Neurology) will be responsible for corresponding with NIH. In addition to providing timely reports to NIH, regarding (i) Unanticipated problems or unexpected serious adverse events that may be related to the study protocol, (ii) IRB-approved revisions to the study protocol that indicate a change in risk for participants, and (iii) Notice of any actions taken by the IRB or regulatory bodies regarding the research and any responses to those actions, the contact PI will be responsible for: Reviewing all CRC screening questionnaires and assessments by participants at baseline, 3-, 6-, and 12-months; and reviewing rates of participant referral to treatment.

The Multiple-Principal Investigator (Ichan School of Medicine at Mount Sinai) will provide site oversight by auditing CHW protocols and church sites where the intervention and control programs will take place. In addition to intervention fidelity monitoring, the co-PI will perform random interviews with CHWs (at least once at each church site) to evaluate the presence of any adverse reactions to the curriculum that may not be captured by questionnaire data.

The DCC will regularly review program data, which will be discussed with the MPIs monthly. The Project Director (PD) will be present on site at every intervention and control program. In addition to project management activities such as recruitment, consenting, training, and data collection, the PD will be responsible for identifying and reporting any adverse encounters - related or unrelated to the intervention – to the Multi-PIs. These include adverse emotional responses, interpersonal conflicts, physical accidents or any other participant safety concerns that may occur during the intervention.

### Composition of the data monitoring committee, its role and reporting structure {21a}

#### Data safety monitoring plan

In compliance with NIH requirements, we will establish a data and safety monitoring plan (DSMP). The purpose of these plans is to ensure the safety of participants and the validity and integrity of the data. Considering the study rationale, population, procedures, and the risk: benefit profile as outlined; the overall risk level for participation in this screening intervention is classified as minimal. Due to the classification of this study as minimal risk, the members of the investigative team described below will serve as the Data Safety Monitoring Committee and will perform the monitoring.

### Adverse event reporting and harms {22}

Diligent study safety monitoring will be conducted by the co-Investigators outlined in the monitoring entity section. Although the risks associated with this research is minimal, we will monitor the effects of the study on adverse participant emotions related to distress or stigma from being questioned about personal mental health concerns. The Project Coordinator / Director will identify adverse events through direct observation and survey response data.

The Project Coordinator will review the circumstances to determine whether institutional notification is necessary. The study Contact-PI, will assume reporting responsibilities for all adverse events to the Columbia University IRB and NIH, which have the authority to halt the trial if it perceives that harm is occurring due to the intervention. Additionally, per Columbia’s IRB policy, all participant deaths, protocol deviations, complaints about the research, and breaches of confidentiality are reportable events.

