The final component of SBIRT involves actual referrals for CRC screening. This begins with a determination of the individual’s health insurance status. Persons without insurance will be enrolled with the assistance of CHWs (who are certified New York State Insurance Navigators) into New York State health plans (insurance exchange or Medicaid). Individuals who are ineligible for health insurance will be referred to our network of local clinics providing CRC screening services regardless of the ability to pay. CHWs will secure a gastrointestinal (GI) clinic appointment for subjects who are guideline discordant for CRC screening within four weeks of the assessment (average appointment lag time within our referral networks). CHWs will refer subjects to our network of GI clinics based on subject preference and insurance status. They will also place a reminder call on the day before the appointment. We will be partnering with Harlem Hospital to screen participants for CRC.

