### Provisions for post-trial care {30}

This study is classified as minimal risk and therefore, there are no anticipated harm to the participants as a result of participating in this study. There are no plans for direct provision of post-trial care.

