### Outcomes {12}

This cluster RCT will evaluate the impact of a CHW enhanced CRC screening intervention on screening uptake (clinic-based colonoscopy or home-based stool test) (primary outcome). The definition of screening uptake is the subject’s self-report of completing a CRC screening test plus the research team’s verification of this completion from medical records. The secondary outcomes include the effect of the CAP program on DIS and on changes to CVD risk captured by LS7 scores. Secondary outcomes will be measured using a modified Block Food Frequency Questionnaire (FFQ)^47^ and Life’s Simple 7 measure, respectively. The FFQ contains a food list of 83 food items that asks about eating habits in the past month, provide estimates of dietary intake, and rank individuals along the distribution of intake. Pictures are provided to enhance accuracy of quantification of portion sizes. The FFQ is intended for either self- or interviewer-administration and has been validated in studies.^35^ RAs will collect FFQ data at baseline, 3- and 6-months. The LS7 measure is based on 7 domains: 3 health physiological metrics (glucose, cholesterol, and blood pressure levels) and 4 health behavior-related metrics (body mass index, physical activity levels, diet quality, and cigarette smoking). Each factor is comprised of items that are rated at “ideal”, “intermediate” or “poor”, corresponding to a score of 2, 1, or 0 respectively. LS7 scores range from 0 to 14 and are calculated from the composite of the factor scores. CVD health is then classified as inadequate (0–4), average (5–9), or optimum (10–14). Achieving a greater number of ideal LS7 metrics is associated with lower risk of dying after stroke and all cause cardiovascular mortality in a dose dependent manner.^91,92^ RAs will collect LS7 measures at baseline, 6-months, and 1-year in the church with standard approaches and FDA approved validated point of care testing (POCT) devices for glucose and cholesterol.

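### The harms section names a harm that does not fit this trial, and its stated sources include no systematic, equal-by-arm ascertainment of complications of the screening tests the intervention promotes

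*Protocol article*

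**What the plan says.** The section Adverse event reporting and harms {22} calls the risks minimal and then names one thing to be monitored: "adverse participant emotions related to distress or stigma from being questioned about personal mental health concerns". It gives the method of detection: "The Project Coordinator / Director will identify adverse events through direct observation and survey response data". It adds that, under the institution's IRB policy, "all participant deaths, protocol deviations, complaints about the research, and breaches of confidentiality are reportable events".

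The section on the coordinating center and steering committee {5d} is wider. The Project Director, on site at every intervention and control program, reports adverse encounters. The examples given include emotional responses and "interpersonal conflicts, physical accidents or any other participant safety concerns that may occur during the intervention". The contact principal investigator reports to NIH on "Unanticipated problems or unexpected serious adverse events that may be related to the study protocol".

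On where the tests happen, the SBIRT description says "CHWs will refer subjects to our network of GI clinics based on subject preference and insurance status", and it names a partner hospital. The Outcomes section {12} counts a clinic colonoscopy or a home stool test. It defines uptake as self-report "plus the research team’s verification of this completion from medical records".

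On expected risk, the post-trial care section {30} says that "there are no anticipated harm to the participants as a result of participating in this study". The data safety monitoring plan section {21a} classifies overall risk as minimal and, for that reason, makes the investigative team its own monitoring committee.

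**The concern.** The harms item is filled in, but with a target that belongs elsewhere. SBIRT was, by the protocol's own account, first designed for people at risk of mental disorders, and the named harm fits that origin better than its use here. The participants are asked about screening history, diet, discrimination, trust in healthcare and stress.

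Meanwhile the intended effect of the intervention is more completed screening tests. Community health workers (CHWs) secure a GI appointment and make a reminder call, so these tests lie on the causal path from allocation to the primary outcome. Any complication would tend to be more frequent in the intervention arm simply because more tests are done there. If such events are found only when someone happens to mention them, the trial would report its benefit by arm without a comparable count of the matching harm. The bodies that may halt the trial would also have no systematic feed of these events.

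**Working it through.** The protocol states no figure for harms, so there is none to reproduce. The check sets the sections side by side and then gives the scale.

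**1. Named harm against trial content.** Table 1 lists no mental-health instrument beyond a perceived stress scale. It does list an everyday discrimination scale and a healthcare trust scale. Distress from questioning is therefore plausible; describing it as arising from mental-health questions is what does not fit.

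**2. Stated sources against where tests happen.**
- Direct observation covers the church program, where study staff are present. Clinic, hospital and home are outside it.
- Survey responses cover the instruments in Table 1. None is labelled as an adverse-event, complication or unplanned-care measure. At 12 months the table marks only the biometric Life's Simple 7 measures, the food questionnaire and physical activity.
- Medical records are opened at 6 months, for reported tests, with completion as the stated purpose.
- The Project Director's remit covers other safety concerns, but ties them to the time of the intervention.

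No stated source systematically looks for a complication of a screening test.

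**3. Contact by arm.** The intervention arm has up to 6 motivational sessions. It then has coaching weekly for 4 weeks and every two weeks for 8 weeks, which is 4 + 8/2 = 8 sessions. That makes up to 6 + 8 = 14 described CHW contacts. The usual-care arm is described as receiving brochures, a list of screening sites and a resource guide after baseline. Spontaneous reports have many more chances to surface in the intervention arm.

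**4. Scale.** Inputs from the Aim 1 power section: 220 per arm, 198 after 10% attrition, a target difference of 0.15, and usual-care rates of 0.20 to 0.50.
- Extra completed tests: 0.15 × 220 = 33 (0.15 × 198 = 29.7).
- Usual care: 0.20 × 220 = 44 to 0.50 × 220 = 110.
- Intervention: 0.35 × 220 = 77 to 0.65 × 220 = 143.

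These are completed tests of any kind. The colonoscopy share is not given, so 77 to 143 is an upper limit on intervention-arm colonoscopies among completers.

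**5. What full capture could show.** The protocol gives no complication rate. Assume r between 0.1% and 1% per procedure, for illustration only, and let every completed test be a colonoscopy.
- Expected events, N × r: 77 × 0.001 = 0.08 to 143 × 0.01 = 1.4.
- Chance of at least one, 1 − (1 − r)^N: 7% (N = 77, r = 0.1%) to 76% (N = 143, r = 1%).
- Upper 95% bound after zero events, 1 − 0.05^(1/N): 3.8% (N = 77) to 2.1% (N = 143).

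Even complete ascertainment would describe harm and hardly test a difference between arms.

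**The case against.** The strongest reply is that this is an article. The full protocol and the data and safety monitoring plan are not shown, and form-level content belongs there. Table 1 gives instrument names, so a complication question could sit inside one of them. That stands as a limit on the finding: the omission alone would not be a point. What remains is that the article does fill in the harms item, with a target that does not match the trial and with sources that leave out the tests it promotes.

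A second reply is that colonoscopy here is guideline-recommended care delivered by outside clinics, not a study procedure. That is true, but the intervention arranges the appointment and the completed test is the primary outcome.

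Four stronger readings are tempting, and the protocol does not support them.
- A reader might infer that the monitoring cannot detect procedural complications at all. Deaths, complaints and unexpected related serious events are reportable, the contact principal investigator reviews the assessments, and record verification could reveal a complication incidentally.
- A reader might infer that only mental-health distress is monitored. The oversight section also covers accidents and other safety concerns. Its closing phrase on timing could even be read as the whole intervention period, which would take in many clinic visits.
- A reader might infer that the trial plans to conclude that harm is minimal. Minimal is a risk classification made in advance; no safety conclusion is planned.
- A reader might take the 33 extra tests as 33 extra colonoscopies. They include home stool tests.

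**Conclusion.** The point holds in a limited form. The named harm is mismatched, the harms and oversight sections differ in scope, and neither describes systematic ascertainment, equal by arm, of complications of the promoted tests. Serious events may still surface, but passively and with unequal opportunity: up to 14 described CHW contacts in one arm against a hand-out of materials in the other. An absence of reported procedural harm would therefore carry little information.

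The exposure at issue is up to about 33 additional participants screened per 220. This assumes that the 15-point target is met and leaves the colonoscopy share unknown. The event rates in the working are assumptions. Nothing here affects the primary analysis or the sample size. The unshown monitoring plan may already contain the missing procedure; if so, the harms section still has to be brought into line with it.

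**What to change.** In the harms section, keep the distress item but reword it to refer to the questionnaires actually administered, and add complications of the screening tests as a monitored harm. Reconcile the section with the Project Director's remit in the oversight section, stating what period and which locations that remit covers, and with the data and safety monitoring plan.

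Add one field, worded identically in both arms, to the 6-month record-verification form: whether a complication or unplanned care after the test is recorded. Add the matching question to the 6-month interview by the research assistants, who are blinded, and put it to all participants, because records are opened only for tests reported as completed. Report counts by arm, with the type of test as denominator, as description only. Pass events on through the existing route to the contact principal investigator, the IRB and NIH.

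The cost is a wording change and a field on two instruments already planned, with slightly longer abstraction and some additional reportable events. Recruitment began in March 2023 and is expected to run to 2027. Participants who passed 6 months before the change may lack the field, so the report should give the number assessed in each arm.

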### Frequency and plans for auditing trial conduct {23}

#### Monitoring study safety

The data and safety monitoring plan for this study will include reporting adverse events to the IRB and NIH trials. The Columbia IRB will have the authority to halt the trial if it believes that harm is occurring as a result of the intervention. All non-time sensitive adverse events will be reported to the NIH through yearly progress reports and the final report submitted at the end of year 5 of the study. All study staff will complete the Good Clinical Practice and Human Subject Protection trainings prior to working with participants. Internal monthly quality control audits, periodic assessments of data quality and timeliness, participant recruitment, accrual and retention, and protocol fidelity monitoring will also be executed. During the early stages of enrollment, one or more “Early Safety/Trial Integrity Reviews” will be held to review safety considerations and ensure proper implementation.

### Plans for communicating important protocol amendments to relevant parties (e.g., trial participants, ethical committees) {25}

All protocol amendments will be submitted to the Columbia IRB and if applicable, participants will be notified. Study personnel will submit annual progress reports to the NIH (funder). Breach report forms will be completed to document any deviations from the original study protocol.

### Dissemination plans {31a}

#### Community dissemination

A dissemination symposium will be organized by the Community Coalition at a community-based venue in Harlem. The investigators and selected members of the Coalition will co-present. The symposium will be specifically organized to gather community feedback. The participating churches and stakeholder organizations will have access to the content of the symposium.

#### Study dissemination and implementation

If the SBIRT and ALIVE! interventions are shown to be effective through this trial, our next step will be to design a Hybrid Type 3 Implementation-Effectiveness Study to disseminate and implement the intervention across the community of Black Churches throughout New York State.

## Discussion

Deaths from CRC have steadily declined, although a shift in the patient population towards younger ages has been observed.^62^ Disturbingly, recent trends reveal a 2% increase in incidence and 1% increase in death rates among people younger than 50 years.^4^ Today, 94% of new cases occur in adults 45 years or older,^63^ and by the year 2030, CRC will become the leading cause of cancer-related deaths among those aged 20–49.^64^ Data such as these led the American Cancer Society to lower the recommended age for CRC screening tests from age 50 to age 45 years, while people at high risk (e.g., significant family history) for CRC should consider screening tests before age 45 years. In May 2021, the US Preventative Services Task Force (USPSTF) adopted the lower age recommendations.^3^

Black churches can increase the uptake of evidence-based screening for cancer^65^ and cardiovascular disease.^38^ In urban AA communities, 65–80% attend church regularly,^66^ many of whom are exposed to a church “Health Ministry” of volunteers who provide health education, screening, and resources to community members.^67^ Church-based interventions include the use of digital health applications, which have been conducted successfully and with low attrition rates.^38^

CHWs are trusted community members^68^ trained to function as health educators, health coaches, navigators, care coordinators, case managers, and patient advocates.^69^ CHWs can serve as linkages to clinical care, and reduce barriers related to SDoH including transportation, childcare, and health system navigation. They can support chronic disease detection and management^70, 71^ and increase cancer screening rates^72, 73^ in a cost-effective manner. We hypothesize that utilizing CHWs for church based colorectal cancer screening can support chronic disease detection and management and increase cancer screening rates in a cost-effective manner.

## Trial Status

Protocol version IRB-AAAT9307, May 2, 2023. Recruitment for this study began in March 2023 and is expected to be completed in 2027.

## Figures and Tables

**Figure 1: F1:**
[figure not shown]
Trial Design Overview

**Table 1: T3:** Clinical Measures

Main Measures	Baseline	3-months	6-months	12-months
	**Physiological Measures**			
Biometric Life Simple-7 (blood pressure, A1C, BMI, and cholesterol)	X		X	X
	**Self-Report Measures**			
Socio-Demographics	X		X	
NIMHD PhenX Social Determinants of Health	X		X	
Health Literacy	X		X	
Everyday Discrimination Scale	X		X	
Thompson BQ Healthcare Trust Scale	X		X	
Colorectal Cancer (CRC) Screening Measure	X		X	
Verification CRC Screening Completion			X	
Perceived benefits and barriers of CRC screening	X		X	
Food Frequency Questionnaire	X	X	X	X
Six-Item Food Insecurity Survey	X		X	
CDE Health conditions	X		X	
Health Literacy Newest Vital Signs	X		X	
Perceived Barriers and Benefits	X		X	
Perceived Stress Scale	X		X	
Physical Activity	X		X	X

**Table 2: T4:** SPIRIT Schedule of Enrollment, Interventions, and Assessment

[figure not shown]

## Data Availability

Study related data analyses will be completed by the Data Coordinating Center. All guidelines for sharing data will be followed. Plans for archiving and sharing data will be finalized within 2 years of the end of the study.

## Abbreviations

CRC: Colorectal cancer
U.S.: United States
AAs: African Americans
CHWs: Community Health Workers
SBIRT: Screening, Brief Intervention using Motivational Interviewing, and Referral to Treatment
LS7: Life Simple 7
CVD: Cardiovascular Disease
CFIR: Consolidated Framework for Implementation Research
FBO-CI: Faith-Based Organization Capacity Inventory
FIT: Fecal Immunochemical Test
gFOBT: guaiac fecal occult blood test
sDNA: stool DNA test
CT: computed tomography
RAU: Referral as Usual
CAP: Culturally-adapted ALIVE! Program
CBPR: community-based participatory research
RAs: research assistants
TIC: trauma-Informed Care
MI: motivational interviewing
OARS: open-ended questions, affirmations, reflections, and summary statements
GI: gastrointestinal
RE-AIM: reach, effectiveness, adoption, implementation, maintenance
DIS: Food Frequency Questionnaire FFQ Dietary inflammatory score
POCT: point of care testing
PC: project coordinator
DCC: Data coordinating center
CRF: case-report form
ITT: intent-to-treat
PD: project director
DSMP: data and safety monitoring plan
USPSTF: US Preventative Services Task Force
NCI: National Cancer Institute
EBCCP: Evidence-Based Cancer Control Programs
DIS: Dietary Inflammatory Score
DII: Dietary Inflammatory Index
IMB: Information-motivation-behavioral
CDC: Center for Disease Control and Prevention
